**3.1.3 Handling of Patients**

1) The investigator will provide an adequate explanation about participation in this study, and will obtain consent from participants.

2) If some mucosal damage is observed on small intestinal endoscopy, the investigator will confirm that the subject satisfies the inclusion criteria and does not meet the exclusion criteria, and will register the subject into the study.

**3.1.4 Registration Method**

Central registration system

1. The investigator will fill out the registration communication form in accordance with the registration procedure and register the subject to the central registration center (see below) by fax.

Central registration center: Medical Division, Kondo Photo Process Co., Ltd.

[name]

1. The central registration center will confirm whether the subject is eligible for this study.

• If the subject is eligible, a subject number—“(study site code), (registration number)”—will be assigned. The central registration center will specify that “the subject can be registered,” write the subject number in the registration confirmation form, and send the form to the investigator by fax.

• If the subject is not eligible, the central registration center will specify that “the subject cannot be registered,” write the reason in the registration confirmation form, and send the form to the investigator.

• The central registration center will retain all registration forms sent by fax.

1. The investigator will confirm the contents of the registration confirmation forms returned from the central registration center by fax.

• If the subject is registered, the fact that “the subject was registered” and the registration number will be specified in the subject screening list.

• If the subject is not registered, the fact that “the subject was not registered” will be specified in the subject screening list and the study will be completed at that time.

1. The investigator will retain all registration confirmation forms sent by fax.

**3.2 Study Design**

Classification based on the method of administration of the drug: A randomized, double-blind, placebo-controlled study.

Classification based on the contents of the study: A study to explore drug effect.

**3.3.1 Study Drug and Instrument Used**

Generic name: Rebamipide

Capsule endoscope (Given Image Diagnosis System manufactured by Given Imaging Ltd.)

**3.3.2 Test Drug**

(1) Generic name: Rebamipide

(2) Dosage form: White film-coated tablet

(3) Strength: One tablet = 100 mg rebamipide

(4) Storage: Room temperature

**3.3.3 Control Drug**

(1) Placebo

(2) Dosage form: Lactose

(3) Strength: One tablet = 100 mg lactose

(4) Storage: Room temperature

**3.3.4 Concomitant Drugs**

1) As described in the exclusion criteria in 3.1.3, drugs that affect the degree of small intestinal mucosal damage will be prohibited in principle during the study.

2) Drugs other than the above-mentioned prohibited concomitant drugs that have been used since before the initiation of administration of rebamipide can be concomitantly used as long as the dose is maintained constant during the study.

3) If patients with active gastric ulcer and duodenal ulcer are treated, an antisecretory drug (proton pump inhibitor, omeprazole) should be administered as necessary. However, mucosal protectants such as rebamipide should not be administered.

4) In patients taking mucosal protectants, the drugs should be discontinued by 2 weeks before capsule endoscopy.

5) If drugs other than the study drug are used, the drug name, dose, and administration period should be entered in the investigation form.

**3.3.5 Method and Period of Administration**

1) Patients with small intestinal damage among those taking Bayaspirin will be randomized into two groups (groups A and B). Capsule endoscopy will be used in the diagnosis of the small intestine. A separately specified controller will perform the allocation.

2) Randomization

Subjects will take the randomly assigned test drug during the study.

Dynamic allocation by using the minimization method will be applied in randomization, and subjects will be allocated to each of the two groups in the study. Drug numbers and information on the allocated groups will be managed by the allocation controller, and will be disclosed when the data are fixed after the completion of the study.

3) Allocated groups and drug administration method:

Group A: Three tablets per dose of control (placebo) tablet (100 mg lactose) will be taken three times daily after every meal.

Group B: Three tablets per dose of rebamipide tablet (100 mg rebamipide) will be taken three times daily after every meal.

4) Administration period: 8 weeks

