**3.4 Evaluation Criteria**

**3.4.1 Primary Endpoint**

Decreasing the number of small intestinal mucosal breaks

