**3.7 Statistical Analysis**

**3.7.1 Analysis Method**

**3.7.1.1 Analysis of the subjects’ background before the initiation of the study**

Results are expressed as medians and interquartile ranges for continuous variables and percentages for categorical variables. The characteristics of patients in the placebo and rebamipide groups were compared using the χ2 test or Fisher exact test for categorical variables, whereas quantitative variables were analyzed by the Mann–Whitney U-test. The Wilcoxon signed-rank test (for continuous data) or McNemar test (for ordinal data) was used for comparisons of data between baseline and 8 weeks. Differences with P-values <0.05 were considered significant.

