**3.7.1.2 Method of analysis of the primary and secondary endpoints**

The Wilcoxon signed-rank test (for continuous data) or McNemar test (for ordinal data) was used for comparisons of data between baseline and 8 weeks. Differences with P-values <0.05 were considered significant.

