**3.7.1.4 Sample size**

Sample size was estimated based on a previous study showing that the complete healing rate of LDA-induced mucosal breaks was 58% in patients who took misoprostol, a PGE1 analog, for 8 weeks. The following assumptions were made for sample size calculation: (1) the wound-healing effect of a triple dose of rebamipide was equal to that of misoprostol; (2) the complete healing rates in the placebo and rebamipide groups were 20% and 58%, respectively; (3) 10% of patients in each group will either drop out or have unsatisfactory follow-up VCE images. We calculated that at least 30 patients were needed in the rebamipide group to give the study 90% power at a 5% significance level by a test of proportions.

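### Patients are allocated by minimization, but no stated test uses the minimization factors; an unadjusted between-arm test added to repair 3.7.1.2 would be conservative and lose power if a factor is prognostic

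*Protocol*

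**What the plan says.** - **Allocation (Protocol 3.3.5, item 2).** "Dynamic allocation by using the minimization method will be applied in randomization". The factors are not named.
- **Endpoint analysis (3.7.1.2).** "The Wilcoxon signed-rank test (for continuous data) or McNemar test (for ordinal data) was used for comparisons of data between baseline and 8 weeks". These are before-after comparisons without a covariate or stratum. No comparison of the two arms on an endpoint is stated.
- **Between-arm tests (3.7.1.1).** "The characteristics of patients in the placebo and rebamipide groups were compared using the χ2 test or Fisher exact test for categorical variables", with Mann-Whitney for quantitative variables. They appear under the analysis of subjects' background and are also unadjusted.
- **Primary endpoint (3.4.1).** "Decreasing the number of small intestinal mucosal breaks". Complete healing is the first secondary endpoint (3.4.2).
- **Sample size (3.7.1.4).** A plain test of proportions, assuming that "the complete healing rates in the placebo and rebamipide groups were 20% and 58%, respectively" and that "10% of patients in each group will either drop out or have unsatisfactory follow-up VCE images". The design figure in 3.3.6 shows 15 placebo and 30 rebamipide patients.

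**The concern.** Minimization forces the arms to be alike on chosen factors. If a factor predicts outcome, that balance removes its contribution from the true variability of the difference between arms. An unadjusted test still counts the contribution in its standard error. The standard error is then too large, the true type I error falls below the nominal 5%, and power is lost.

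The protocol is placebo-controlled and sized on a between-arm comparison, so 3.7.1.2 will have to acquire a between-arm test. The nearest tests to borrow are the unadjusted ones in 3.7.1.1, and borrowing them would create this mismatch. In a trial of about 45 patients, several points of power are worth keeping.

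**Working it through.** **1. The plan's own figure.** With 1:1 allocation, a one-sided 5% test and mean proportion (0.20 + 0.58)/2 = 0.39, n per arm = [1.645·√(2·0.39·0.61) + 1.2816·√(0.20·0.80 + 0.58·0.42)]² / 0.38² = 26.3, rounded up to 27; 27/0.9 = 30. The figure of 30 therefore comes back for 1:1 and one-sided testing. It also comes back for 1:1, two-sided, unpooled variance and no dropout (29.4, rounded to 30). With the 15:30 design and a two-sided test, the pooled proportion is (15·0.20 + 30·0.58)/45 = 0.453, the null SE 0.157 and the alternative SE 0.137, so power = Φ[(0.38 − 1.96·0.157)/0.137] = 70% (65% after 10% dropout). That shortfall is a separate matter. It matters here only because it leaves no power to spare.

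**2. Size of the mismatch, by formula.** Let R² be the share of outcome variance explained by the minimized factors. With perfect balance the true SD of the difference is √(1 − R²) times what the unadjusted test assumes. The true two-sided error is then about 2·[1 − Φ(1.96/√(1 − R²))]:

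| R² | 1.96/√(1 − R²) | True error |
|---|---|---|
| 0.10 | 2.07 | 3.9% |
| 0.25 | 2.26 | 2.4% |
| 0.40 | 2.53 | 1.1% |

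**3. Simulation, continuous outcome.** Assumptions: 40 evaluable patients; 2:1 minimization on one binary prognostic factor and a four-level non-prognostic site factor, with probability 0.9 of the balancing arm; normal outcome; 4,000 trials per setting. The Monte Carlo SE at 5% is √(0.05·0.95/4000) = 0.3 points. Rank ANCOVA adjusts for the prognostic factor.

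| R² | Mann-Whitney true error | Power at 0.8 SD, unadjusted | Power at 0.8 SD, rank ANCOVA |
|---|---|---|---|
| 0.10 | 3.6% | 60% | 65% |
| 0.25 | 2.5% | 62% | 73% |
| 0.40 | 1.3% | 61% | 82% |

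Rank ANCOVA kept its error between 4.8% and 5.3%. With no prognostic factor, power was 61% against 62%. The errors agree with step 2.

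**4. Second simulation, different set-up.** 45 patients, 1:2 minimization on two binary factors, linear-model adjustment. At R² = 0.3 the mean unadjusted SE was 0.315 against a true SD of 0.271, and 0.315/0.271 = 1.17, so about 17% too wide. Mann-Whitney rejected 2.3% under the null. With simple permuted allocation instead, the unadjusted t-test rejected 5.1%, so the loss of level comes from minimizing and then not adjusting.

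**5. Complete healing, 20% v 58%.** Same set-up, with an assumed odds ratio per factor:

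| Odds ratio | Power unadjusted | Power adjusted |
|---|---|---|
| 1 | 71% | 71% |
| 2.5 | 70% | 74% |
| 5 | 71% | 79% |
| 8 | 73% | 84% |

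The adjusted figures come from a linear model with both factors. A stratified test was not simulated.

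**6. Sparseness.** Expected placebo healers: 15 × 0.9 × 0.20 = 2.7. Splitting these by site and by baseline category would leave most cells empty.

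**The case against.** **The criticised test is not in the plan.** A reader might infer that following 3.7.1.2 as written yields the error rates above. The protocol does not support that. Its endpoint tests are before-after comparisons, and the rates above are for a between-arm test. If each patient's change is symmetric about zero, the signed-rank test is exact however patients were allocated. Under a different assumed null, in which factor levels change in opposite directions, a within-arm test was mildly conservative (2.5% to 4.5% for R² of 0.1 to 0.4), but the protocol gives no basis for that null. The objection stands, and the point is conditional on how the missing comparison is supplied.

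**Factors and adjustment are often left to the SAP.** This stands for the naming of the factors, which is not a fault of the protocol. It does not wholly answer the rest: 3.7.1.2 and 3.7.1.4 do name tests, and all are unadjusted.

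**The benefit of balancing is not simply thrown away.** A reader might infer that it is. At R² = 0.3 and a 0.9 SD effect in the second simulation, power was 79% without minimization, 84% with minimization and no adjustment, and 92% with both. Only part of the gain is forgone.

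**The error is on the cautious side, in a study that calls itself exploratory.** This is correct. The mismatch does not raise the false-positive risk. The cost is power and precision.

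**The size cannot be derived from the document.** This also stands. The upper figures need a single factor explaining 40% of variance in a normal outcome, whereas the endpoint is a change in a count.

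**Conclusion.** The point holds as a conditional one. The protocol allocates by minimization and names no test that uses the minimization factors. If the missing between-arm comparison is supplied by an unadjusted Mann-Whitney or chi-square test, that test will be conservative whenever a factor is prognostic. For R² of 0.1 to 0.4 the power forgone at 0.8 SD is about 5 to 21 points (65 − 60 to 82 − 61); if no factor is prognostic it is nil. These sizes rest on assumed prognostic strength, 2:1 minimization, 40 evaluable patients and a normal outcome.

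The absent between-arm endpoint comparison in 3.7.1.2 is the more serious fault and should be raised separately. This point says what form its repair should take. It is a cheap improvement and gives no reason to think the planned analysis would produce false positives.

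**What to change.** In 3.7.1.2:

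1. Make the between-arm analysis of the break count a rank ANCOVA that includes the minimization factors actually used. If site is one of them, pool small sites.
2. For complete healing, adjust only for the main prognostic factor, for example by a stratified test on baseline break category if that is among the factors. Do not also stratify by site, because fewer than three placebo healers are expected.

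The factor list may sit in 3.3.5, the allocation procedure or the SAP, provided that the analysis refers to the same list.

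Cost: one or two sentences and a few degrees of freedom, with no extra patients or data. The number of sites is not given, so the pooling rule should be set before unblinding.

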**3.3.6 Contents and Schedule of Examination**

**Study design**

**Group A**

**(n=15)**

**Group B**

**(n=30)**

**Ｃａｐｓｕｌｅ　ｅｎｄｏｓｃｏｐｙ**

**pre**

**Ｂｌｏｏｄ　ｔｅｓｔ**

**Objective symptom**

**4 weeks**

**8 weeks**

**Ｓｕｂｊｅｃｔｉｖｅ　ｓｙｍｐｔｏｍ**

**3.3.6 Observation Items**

Subject background: Specified at registration

ID assigned by randomization, date of birth, sex, height, body weight, body mass index, drinking history (years), smoking history (years), underlying disease, complications, and used drugs (drug name, dose, and period of use)

Treatment compliance: Status of the administration of the drug

Hematology: Before administration, after administration (4 weeks), and at the completion of treatment (8 weeks)

Red blood cells (104/μL), white blood cells (104/μL), hemoglobin (g/dL), albumin (g/dL), hematocrit (%), total protein (g/dL), glutamic oxaloacetic transaminase (IU/L), glutamic pyruvic transaminase (IU/L), blood urea nitrogen (mg/dL), creatinine (g/day), iron (μg/dL), and C-reactive protein (μg/dL)

Subjective and objective symptoms: Before administration, after administration (4 weeks), and at the completion of treatment (8 weeks)

Subjective symptoms: Epigastric pain, abdominal distension, anorexia, heartburn, stomach heaviness, nausea, vomiting, belching, etc.

Objective symptoms: Epigastric tenderness, hematemesis, melena, etc.

Small intestinal endoscopy: Before administration and at the completion of treatment (8 weeks)

Stool frequency, abdominal symptoms, etc. (after examination; abdominal symptoms and capsule excretion symptoms will be confirmed)

**3.4 Evaluation Criteria**

**3.4.1 Primary Endpoint**

Decreasing the number of small intestinal mucosal breaks

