**3.4.2 Secondary Endpoints**

1) Complete healing of small intestinal mucosal breaks

2) Improving the Lewis score

3) Improving hemoglobin and albumin levels

4) Safety evaluation

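### The stated 90% power belongs to complete healing, a secondary endpoint; the primary endpoint, the number of mucosal breaks, has no power basis

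*Protocol*

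**What the plan says.** All references are to the protocol.

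- Section 3.4.1 gives a single primary endpoint: "Decreasing the number of small intestinal mucosal breaks".
- Section 3.4.2 puts "Complete healing of small intestinal mucosal breaks" first among the secondary endpoints.
- Section 3.7.1.4, the only text on sample size, starts from the healing rate seen with misoprostol in an earlier study. It assumes that "the complete healing rates in the placebo and rebamipide groups were 20% and 58%, respectively" and that "10% of patients in each group will either drop out or have unsatisfactory follow-up VCE images". Its conclusion reads "at least 30 patients were needed in the rebamipide group to give the study 90% power"; the underlying comparison is of two proportions, with the significance level set to 5%. It states neither whether the test is one- or two-sided nor the size of the placebo group.
- The study design diagram in section 3.3.6 gives the group sizes: 15 in Group A (placebo) and 30 in Group B (rebamipide).
- Section 3.7.1.2 names, for the primary and secondary endpoints, only comparisons over time: "The Wilcoxon signed-rank test (for continuous data) or McNemar test (for ordinal data) was used for comparisons of data between baseline and 8 weeks".
- Section 2 describes the study as a pilot, and sections 1 and 3.2 call it exploratory.

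**The concern.** A reader who sees 90% power claimed for a study takes it to refer to the primary endpoint. Here it refers to another variable. The number of breaks is a count, or a change in a count; complete healing is yes or no. A patient who goes from 20 breaks to 2 has a large primary response and is a healing failure. A patient who goes from 1 to 0 is a healing success with a small change in count. Section 3.1.1 asks only for small intestinal damage on capsule endoscopy and sets no minimum number of breaks, so baseline counts may differ widely. Power for one endpoint therefore cannot be read across to the other.

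What is at stake is how the result is read. A null result on the number of breaks could be taken as coming from a study with a 10% chance of missing the assumed effect, when the protocol offers no basis for any such figure.

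**Working it through.** **1. Where the 30 comes from.** Inputs from section 3.7.1.4: 20% v 58%, 5% level, 90% power, 10% loss. Assumed, because not stated: one-sided test, equal groups, pooled variance under the null, no continuity correction.

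n per group = [1.645 × √(2 × 0.39 × 0.61) + 1.282 × √(0.20 × 0.80 + 0.58 × 0.42)]² / 0.38²
= [1.645 × 0.690 + 1.282 × 0.635]² / 0.1444 ≈ 26.3, so 27.

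Allowing for loss: 27 / 0.90 = 30. The figure of 30 is thus reproduced from the healing rates alone; nothing about the number of breaks is needed. The two-sided version gives 33 per group, or 37 with loss.

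**2. Power for healing at the planned 15:30.**

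Pooled rate = (15 × 0.20 + 30 × 0.58) / 45 = 0.453.
SE under the null = √(0.453 × 0.547 × (1/15 + 1/30)) = 0.157.
SE under the alternative = √(0.16/15 + 0.2436/30) = 0.137.

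- Two-sided: Φ((0.38 − 1.96 × 0.157) / 0.137) = Φ(0.52) ≈ 70%.
- One-sided: Φ((0.38 − 1.645 × 0.157) / 0.137) = Φ(0.88) ≈ 81%.

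After 10% loss, 30 becomes 27 and 15 becomes 13.5, taken as 13 or 14. The same formula gives:

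| Placebo v rebamipide | Two-sided 5% | One-sided 5% |
|---|---|---|
| 15 v 30 | 70% | 81% |
| 14 v 27 | 66% | 78% |
| 13 v 27 | 64% | 76% |

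Exact enumeration of the chi-square test agrees within about 2 percentage points. None of these figures reaches 90%.

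**3. The primary endpoint.** The protocol gives no expected change and no SD for the number of breaks, so its power cannot be computed. Only illustrations are possible, and both below assume a between-group test at two-sided 5%, which section 3.7.1.2 does not name for the endpoints.

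Normal approximation, detectable difference in SD units = (1.96 + z) × √(1/n₁ + 1/n₂):

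- 14 v 27: √(1/14 + 1/27) = 0.329; 2.802 × 0.329 = 0.92 SD for 80% power; 3.242 × 0.329 = 1.07 SD for 90%.
- 13 v 27: √(1/13 + 1/27) = 0.338; the results are 0.95 SD and 1.09 SD.

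Rank scale (Noether), power = Φ(√(12c(1 − c)N) × (p − 0.5) − 1.96). Here c is the placebo share, N the total, and p the probability that a rebamipide patient does better than a placebo patient. For 13 v 27, √(12 × 0.325 × 0.675 × 40) = 10.26, so power is 54% at p = 0.70, 73% at 0.75 and 87% at 0.80. The values of p are assumed.

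**The case against.** The strongest reply is that this is a pilot. A pilot need not have formal power for its primary endpoint, and sizing it on the one relevant earlier result is a recognisable choice. That stands, and it limits the weight of the point. It does not remove it, because section 3.7.1.4 does not describe the size as a pilot choice. It claims 90% power at a 5% level, and section 3.7.1.2 calls results significant at P < 0.05.

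Two stronger readings are tempting, and the protocol supports neither.

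- A reader might infer that the mismatch lets the authors lead with whichever endpoint succeeds. Sections 3.4.1 and 3.4.2 fix the order: one primary endpoint, with healing secondary. Sizing on another variable changes neither that order nor the type I error.
- A reader might infer that the primary endpoint must have less power than healing. That cannot be shown without an effect and an SD, and it may be false. Suppose the number of breaks follows a latent normal variable cut off at zero with equal variances. Then 20% v 58% healed implies a shift of 0.84 + 0.20 = 1.04 SD. In simulation at the planned and evaluable sizes, a rank test on the counts then has about 81–85% power, against about 66–70% for healing. Other models may give the opposite.

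It is also fair to say that SD units suit a count with many zeros poorly, so the figures of 0.92–1.09 SD are only a guide.

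**Conclusion.** The point holds as a mismatch within the protocol. The 90% in section 3.7.1.4 was derived for complete healing, secondary endpoint 1, and does not apply to the primary endpoint, for which no effect size, variance or test was used. Whether the primary endpoint is well or badly powered is unknown from this document.

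The 90% also fails for healing at 15:30, where power is about 70% two-sided or 81% one-sided before loss and about 64–66% or 76–78% after it. These figures rest on the protocol's own rates and loss, a pooled test without continuity correction, and a 5% level whose sidedness is not stated. Given the declared pilot status, this is a correction that should be made, not a flaw that invalidates the design.

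**What to change.** Rewrite section 3.7.1.4 as follows.

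1. Say that the calculation refers to complete healing, secondary endpoint 1, and remove the claim of 90% power for the study.
2. State the sidedness, and give the power for healing that 15:30 delivers: about 70% two-sided or 81% one-sided before loss, and about 64–66% or 76–78% with 13–14 v 27 evaluable.
3. For the primary endpoint, do one of two things. Either say that the size is a pilot choice without formal power for the number of breaks, or add a detectable difference under a named between-group test, marked as illustrative. Under the normal approximation at two-sided 5% with 13–14 v 27, this is about 0.92–0.95 SD for 80% power and 1.07–1.09 SD for 90%. The second choice requires the between-group test to be named for the endpoint as well.

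Relabelling the calculation while keeping the 90%, or making healing primary on the strength of it, would carry forward a figure that 15:30 does not deliver.

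The cost is protocol wording, with no extra patients and no change in conduct. The downside is that the stated power becomes less favourable than 90%.
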